# Risk and benefit of combined moderate and binge drinking on cardiovascular diseases (CVD)

## Objectives

An overall aim of the project is to assess the possible protective effect of moderate alcohol consumption against CVD and which factors moderates such an effect. The study will benefit from a large sample size which will enable us to investigate subgroups of alcohol consumption pattern in more detail than previously done in research.

## Research questions (RQ)

- (1) To investigate the risk and protective effects on CVD morbidity and mortality associated with various combinations of moderate alcohol consumption and binge drinking. We will here also look at risk in the sub-group of patients with pre-existing CVD.
- (2) To investigate if the effects of moderate alcohol consumption and binge drinking on CVD can be explained by or interact with mental distress (depression and/or anxiety).
- (3) To investigate if the effects of moderate alcohol consumption and binge drinking on CVD can be explained by or interact with cognitive ability (IQ), educational level, or other socioeconomic factors.
- (4) First, to investigate how alcohol consumption in family members are related to CVD risk among index individuals. Secondly, to use alcohol consumption among siblings and offspring as instrumental variable to assess the causal effects of alcohol consumption pattern on CVD.
- (5) Using pairs of siblings, monozygotic and dizygotic twins discordant for CVD to estimating the association between moderate alcohol and binge drinking and CVD within families. These results will adjust for early life and family factors.
- (6) To assess familial aggregation of mental distress, alcohol related mortality and CVD morbidity and mortality.

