## 1. Relevance to the call for proposals:

The health effect of alcohol consumption pattern (moderate and binge drinking) is of significant public health relevance because alcohol consumption in Norway and other countries in Northern Europe have been increasing since 2000. Furthermore, the consumption pattern is changing from binge drinking towards moderate regular intake. Norway is in a fortunate position to address this issue because large scale health surveys with data on both moderate and binge drinking have been linked to a multigenerational database, hospital discharge on CVD morbidity and mortality and other registries.

The national policy building upon a premise that total consumption affects number of problem drinkers might be under pressure. An implication of this principle of solidarity is that anyone can potentially experience health problems due to alcohol consumption. However, the scientific evidence base for population wide approaches is challenged for several reasons:

First, the effect of alcohol consumption on CVD appears to be divergent (RQ 1). But also, alcohol consumption might be influenced by underlying factors, which calls for a reconsidering on the issue of human agency in policy formulation. Individual and personal characteristics, such as psychosocial and cognitive, might explain a large and increasing part of the variation in health behavior (RQ 2). It has also been suggested that personal characteristics to an increasing extent explain socioeconomic inequalities in health. A better understanding of vulnerable subgroups in modern society where according to social theorists, the individual is put at an increased responsibility for managing their own health risk, is imperative for developing future health and alcohol policy. And finally, both alcohol consumption and CVD risk tend to be clustered within families (RQ 3&4). This could indicate the scope for early prevention of both harmful alcohol use and CVD.

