But there is surprisingly little evidence on how the CVD risk associated with alcohol interact with psychosocial factors, such as cognitive ability and mental distress. An editorial stated that: "...the area of research is considered fragmented to the extreme...conducted in a wide range of disciplines (e.g. anthropology, biology, chemistry, economics, history, law, medicine, neurology, psychology, sociology)". Thus, plausible explanations on effects are theoretically grounded in several fields of knowledge. Our project and team aims explicitly to exploit this interdisciplinary challenge.

We recently showed that a substantial part of the educational gradient in both CVD and alcohol related mortality could be explained by family factors early in life shared by siblings. This could indicate that risk factors for CVD and alcohol use share common origin

from childhood onwards, and that some of the estimated effect size both for moderate and binge drinking may be explained by early life confounding or family factors. Few family and life course studies have investigated alcohol and CVD jointly.

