Data analysis: For time to event outcomes such as morbidity and mortality the primary modelling strategy is to use Cox proportion hazard regression models. In RQ 1 the effect of moderate alcohol consumption will be analysed by adjusting for binge drinking and across strata of binge drinking (interaction term will be fitted to formally test if the effect differs). In RQ 2-3 the same strategy will be employed using strata of cognitive ability and mental health. In RQ 4 the aim is to see if using alcohol consumption among family members as instrumental variable will reproduce a protective effect of moderate alcohol consumption as seen in conventional analysis. Using instruments, it will also be possible to estimate the effect sizes and compare the effect and pattern in CONOR participants with that of their sibling. To achieve this, z-scores will be calculated based on units of alcohol consumption reported. For RQ 5, the effects of alcohol consumption will be estimated by comparison between siblings or co-twins ("fixed effect"). This approach effectively matches out all factors shared between siblings that may confound the effect of alcohol on cardiovascular mortality reported in studies of unrelated individuals. The analyses will be conducted in the statistical software STATA. Age, smoking status and number of cigarettes per day in smokers, physical activity, self-reported disease (CVD, diabetes, antihypertensive medication) and psychosocial distress at baseline will be adjusted for as potential confounders. In

familial aggregation analysis, we will estimate to what extent alcohol related mortality co-occur in first degree family members with CVD morbidity and mortality and mental distress by summing up number of family members with any of these traits.

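### RQ 4's family instrument cannot separate a causal effect of drinking from the shared family confounding that the protocol itself says may exist

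*Protocol*

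**What the plan says.** The Research questions section gives RQ 4 two parts. The first relates family members' drinking to the index person's CVD risk. The second is "to use alcohol consumption among siblings and offspring as instrumental variable to assess the causal effects of alcohol consumption pattern on CVD". The Statistical methods section gives the test for the second part: whether "using alcohol consumption among family members as instrumental variable will reproduce a protective effect of moderate alcohol consumption as seen in conventional analysis".

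The same protocol describes family sources of both drinking and CVD:

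- The section on relevance to the call states that "both alcohol consumption and CVD risk tend to be clustered within families".
- The Background cites a sibling study in these words: "a substantial part of the educational gradient in both CVD and alcohol related mortality could be explained by family factors early in life shared by" (that is, brothers and sisters). Its comment on this finding is: "This could indicate that risk factors for CVD and alcohol use share common origin". It adds that "some of the estimated effect size both for moderate and binge drinking may be explained by early life confounding or family factors".
- The section on approaches, hypothesis and method says that drinking and cardiovascular risk may have causes in common. It cites heritability of alcoholism and cultural transmission of drinking habits.

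That section defends the instrument on two grounds: it avoids sick-quitter bias, and relatives' intake is less closely tied to the index person's own smoking and diet. It assigns adjustment for shared family factors to the sibling and co-twin fixed-effect analysis. There the instrument and fixed-effect analyses are numbered RQ 3 and RQ 4; in the Research questions and Statistical methods sections they are RQ 4 and RQ 5. The numbering used here is the latter.

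**The concern.** A relative's drinking predicts one's own because relatives share upbringing, environment and genes. The protocol names those same channels as possible common causes of drinking and CVD. If they do affect CVD, the instrument is tied to the outcome by a path that does not run through the index person's drinking, and its independence condition fails.

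The stated criterion does not detect this. Both a true protective effect and shared family confounding in the protective direction would lead the instrument analysis to reproduce protection. The protocol states no independence or exclusion assumption and gives no rule for reading RQ 4 against RQ 5. The listed confounders are age, smoking, physical activity, self-reported disease and psychosocial distress. They do not include the childhood socioeconomic variables listed under Main variables. At stake is the causal conclusion of one of the six research questions, in a project meant to inform alcohol policy.

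**Working it through.** The plan gives no figure to reproduce here, so the check has two parts: a reading of the text and an illustrative model.

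**Text.** Three threats to a causal reading appear in the protocol.

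1. Reverse causation by sick quitters: the instrument addresses it.
2. Confounding by the person's own habits, such as smoking and diet: the protocol claims it is reduced.
3. Shared family and early-life causes: nothing in RQ 4 removes them; RQ 5 is designed to.

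**Model.** Let F be a shared family factor, with all variables below except Y scaled to variance 1 and the true effect of drinking set to zero.

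- Own drinking: A = aF + e
- Relative's drinking: Z = aF + e′
- Outcome: Y = cF + error
- Family correlation in drinking: r = cov(Z, A) = a²

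Then:

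- Ordinary regression bias = cov(A, Y)/var(A) = ac
- Slope of Y on the relative's drinking = cov(Z, Y)/var(Z) = ac
- Ratio (Wald) estimate bias = cov(Z, Y)/cov(Z, A) = ac/a² = c/a
- Ratio bias divided by ordinary bias = (c/a)/(ac) = 1/a² = 1/r

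**Inputs.** The protocol gives neither r nor the size or sign of family confounding. Assumed: r from 0.1 to 0.5 and c = −0.1 (protective direction). The formulas were checked by simulation with 2,000,000 observations per setting.

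| r | Ordinary: formula (simulated) | Ratio: formula (simulated) | 1/r |
|---|---|---|---|
| 0.1 | −0.0316 (−0.0316) | −0.3162 (−0.3207) | 10 |
| 0.2 | −0.0447 (−0.0445) | −0.2236 (−0.2256) | 5 |
| 0.3 | −0.0548 (−0.0531) | −0.1826 (−0.1837) | 3.3 |
| 0.5 | −0.0707 (−0.0709) | −0.1414 (−0.1425) | 2 |

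Protection is reproduced although drinking has no effect. This does not depend on forming a ratio: the slope on the relative's drinking alone carries the same bias, ac, as ordinary regression (simulated −0.0324 to −0.0712).

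**Contrast.** If the confounder is purely individual and not shared with the relative, the simulated ratio estimate is near zero (−0.0052 to −0.0003), while ordinary regression is biased (−0.0947 to −0.0709). The protocol's defence of the instrument is correct for that case.

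**The case against.** The strongest reply is that the rationale is narrower than the wording of RQ 4. The approaches section aims at sick quitters and promises less biased, not unbiased, estimates. Against reverse causation the reproduction test does discriminate, and a failure to reproduce would also be informative. The section pairs the instrument with the fixed-effect analysis and leaves shared factors to the latter. All of this stands. It shows that the problem was recognised, but it does not license the causal wording of RQ 4, and no rule joins the two results.

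Four stronger readings are tempting, and the document does not support them.

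- *The protocol asserts that family factors drive both drinking and CVD.* It does not. Its statements on common causes are hedged with could and may; only clustering is put more plainly, as a tendency. A causal design must still deal with the possibility.
- *The bias must favour protection.* No sign is given. The approaches section speaks of common causes inflating risk, which is the opposite direction. The negative c above is an assumption.
- *The preliminary hazard ratio can be scaled up to size the bias.* The figure of 0.93 (0.88-0.99) compares abstainers with moderate drinkers, so a per-SD first stage does not apply. The accompanying prose says fathers of abstainers have higher risk, whereas 0.93 says lower (the inverse is 1/0.93 = 1.08, with limits 1/0.99 = 1.01 and 1/0.88 = 1.14). That must be reconciled before the figure is used.
- *Standardising intake forces one linear slope and hides a J-shape.* The text says "z-scores will be calculated based on units of alcohol consumption reported". That fixes a scale, not a functional form, which may be left to the analysis plan.

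**Conclusion.** The point holds as a limit on interpretation. If the family causes that the protocol raises as possible are present, relatives' drinking is not a valid instrument for a causal effect. A reproduced protective effect would then count against reverse causation only.

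The size cannot be fixed from the document. The 1/r factor follows from a linear model in which own and relative's drinking load equally on one family factor and nothing else confounds. The range of 2 to 10 rests on the assumed r of 0.5 to 0.1. The planned models are Cox regressions and the protocol does not name a ratio estimator, so these figures illustrate the mechanism and do not predict the study's results. The logical point needs none of them.

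**What to change.** In the Research questions and Statistical methods sections:

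1. Replace the causal claim in RQ 4 with a family-proxy association that informs on reverse causation but is not robust to shared family factors.
2. State the instrument assumptions (relevance, independence, exclusion) and say which of them shared family causes would break.
3. Allow a causal reading only if the RQ 5 within-sibling or co-twin estimate points in the same direction with a compatible interval. The protocol says power within siblings is hard to work out, so a very wide RQ 5 interval should be reported as leaving the question open.
4. In models that use siblings' drinking, adjust for parental class, parental education and housing in childhood, which are already held. This reduces shared confounding but does not remove it.
5. In models that relate offspring's drinking to a parent's CVD, use these variables only in a sensitivity analysis. There they describe the parent's own adult position, which may itself follow from the parent's drinking.

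Separately, reconcile the direction of the preliminary result for fathers with its hazard ratio.

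The cost is wording and model changes on existing data, and a weaker headline claim for RQ 4.

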## 1. Relevance to the call for proposals:

The health effect of alcohol consumption pattern (moderate and binge drinking) is of significant public health relevance because alcohol consumption in Norway and other countries in Northern Europe have been increasing since 2000. Furthermore, the consumption pattern is changing from binge drinking towards moderate regular intake. Norway is in a fortunate position to address this issue because large scale health surveys with data on both moderate and binge drinking have been linked to a multigenerational database, hospital discharge on CVD morbidity and mortality and other registries.

The national policy building upon a premise that total consumption affects number of problem drinkers might be under pressure. An implication of this principle of solidarity is that anyone can potentially experience health problems due to alcohol consumption. However, the scientific evidence base for population wide approaches is challenged for several reasons:

First, the effect of alcohol consumption on CVD appears to be divergent (RQ 1). But also, alcohol consumption might be influenced by underlying factors, which calls for a reconsidering on the issue of human agency in policy formulation. Individual and personal characteristics, such as psychosocial and cognitive, might explain a large and increasing part of the variation in health behavior (RQ 2). It has also been suggested that personal characteristics to an increasing extent explain socioeconomic inequalities in health. A better understanding of vulnerable subgroups in modern society where according to social theorists, the individual is put at an increased responsibility for managing their own health risk, is imperative for developing future health and alcohol policy. And finally, both alcohol consumption and CVD risk tend to be clustered within families (RQ 3&4). This could indicate the scope for early prevention of both harmful alcohol use and CVD.

## **2. Aspects relating to the research project**

### **Background and status of knowledge**

Alcohol has a negative effect on many health-related outcomes but for heart diseases the effects seem to be mixed. Alcohol use is negatively related to hypertensive disease, hemorrhagic stroke and atrial fibrillation. For ischemic heart disease (IHD) and ischemic stroke (cardiovascular diseases, CVD), the relationship is complex. Chronic heavy alcohol use has been associated with adverse cardiovascular outcomes. But light to moderate drinking seems to be related to reduced risk of ischemic diseases.

It is not well understood to what extent frequent episodes of heavy alcohol consumption may counteract the beneficial effect on heart disease and by which mechanisms episodes of heavy alcohol have a negative effect on heart disease. Even rare and occasional episodes of binge drinking seem to increase the risk in a recent study from the northernmost part of Norway. One would expect the protective effect to be more pronounced in individuals who do not binge drink, and not present in individuals who report substantial binge drinking. A recent meta-analysis on binge drinking including only 4718 IHD events gave some support for this notion. Our study will add to this by 6500 CVD cases.

Norwegian studies on adolescent and adult abstainers have shown higher risk of psychosocial factors and might suggest a J-shaped pattern. A general finding is that abstainers tend to have worse health and are poorer. One interpretation of this and similar findings is that since alcohol is such an important token in social interaction, abstainers are likely to differ as a social group and have a wide range of individual characteristics that could put them at increased risk of several health problems. Those who have moderate intake have in studies been shown to have higher cognitive ability compared to abstainers and that heavy drinkers have lower cognitive ability.

But there is surprisingly little evidence on how the CVD risk associated with alcohol interact with psychosocial factors, such as cognitive ability and mental distress. An editorial stated that: "...the area of research is considered fragmented to the extreme...conducted in a wide range of disciplines (e.g. anthropology, biology, chemistry, economics, history, law, medicine, neurology, psychology, sociology)". Thus, plausible explanations on effects are theoretically grounded in several fields of knowledge. Our project and team aims explicitly to exploit this interdisciplinary challenge.

We recently showed that a substantial part of the educational gradient in both CVD and alcohol related mortality could be explained by family factors early in life shared by siblings. This could indicate that risk factors for CVD and alcohol use share common origin

from childhood onwards, and that some of the estimated effect size both for moderate and binge drinking may be explained by early life confounding or family factors. Few family and life course studies have investigated alcohol and CVD jointly.

### **Approaches, hypothesis and choice of method**

The study has some important strengths: the sample size and comprehensive data linkage, the availability of information on both moderate and binge drinking, reasonably long follow-up and linkage to information on both morbidity and mortality. Using morbidity data on hospital discharge on incidences of CVD increases the number of cases by a factor of approximately three to four compared to mortality data, and further increases statistical power further (RQ 1). This enables us to investigate combinations of moderate alcohol consumption and binge drinking. Having clinical endpoints in addition to mortality will be a significant improvement to the literature. It has been suggested that effects of binge drinking could be an artifact due to misclassification or have a non-atherosclerotic pathology.

The study will be able to look into more detail than has previously been possible on the long-term prognosis among patients with preexisting CVD or other high risk subgroups (RQ 1). In terms of drinking patterns, the results of individual level cohort studies mainly apply to cohorts who predominantly drink regularly with few heavy drinking occasions. Adequate power to investigate the combined effect of moderate and binge drinking requires large cohorts with enough data on the distribution of such drinking patterns within a population and information on exposure to other heart disease risk factors, pre-existing CVD as well as cognitive ability, mental distress and family data.

We will in this study be able to investigate if the abstainers might be a selected group more closely, and for a wider range of potential underlying factors, than has previously been done (RQ 2 and 3). An assessment on how these factors relate to alcohol consumption and heart disease will also broaden our understanding on the clinical and public health impact of alcohol in groups at particularly high risk (RQ1 and 2).

The project will use novel approaches by taking advantage of family based designs to understand how both alcohol consumption pattern and CVD risk is patterned across generations and to study how much of the association between alcohol use and CVD may be accounted for by early life socioeconomic environment and shared family factors. Two approaches will be used: *i*) instrumental variable analysis using alcohol consumption among family members as instrument for own consumption and risk of CVD (RQ 3), and *ii*) fixed effect cotwin/sibling analysis (RQ 4) to adjust for shared early life socioeconomic environment and other family factors.

Alcohol consumption and cardiovascular risk may share common causes and artificially inflate estimates of risk. Alcoholism is heritable (heritability 0.52-0.64) and 50 % of the genes involved are shared by full siblings or parents. Several studies suggest that parental alcohol use increases the risk of early alcohol debut and subsequent drinking patterns among children also indicating cultural heritability. Our multigenerational approach investigate if alcohol use and CVD risk is jointly related across generations.

The association between moderate alcohol consumption and CVD mortality resembles the association between body mass index (BMI) and CVD mortality as both have a J-shaped

relationship in which the lowest group (underweight and abstainers) has increased risk compared to those in the moderate categories. Reverse causality by unmeasured health problems may explain this pattern in these groups. In a Swedish intergenerational study, offspring BMI was used as an instrumental variable for own BMI as BMI in the offspring is less likely to be affected by health problems. The authors found less adverse consequences of lower BMI compared to conventional observational studies. Alcohol consumption in family members can be used similarly as instrument for own consumption to avoid the problem of sick quitters potentially producing non-causal increased risk compared to moderate drinkers (RQ 3). In both cases offspring alcohol and BMI are recorded earlier in life whereas CVD in parents is recorded at a higher age. More generally, using family proxies for exposure might be valuable not only to reduce reversed causality, but also because their alcohol intake will be less strongly associated with the individuals' other risk factors that predisposes him/her for CVD, i.e smoking and diet, and give less biased estimates of effect than own alcohol exposure.

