### **Data sources**

The Cohort of Norway (CONOR) Data from 10 epidemiological studies (n=181,891) from 1994-2003 have been merged into a national database. All the surveys included self-reported health and selected diseases, various risk factors, socio-demographic factors, use of medications and physiological measures such as blood pressure, cholesterol, triglycerides, waist and hip circumference, height and weight.

The Norwegian Twin Registry (NTR) Panel II were born 1915-1960. Questionnaires on alcohol consumption were sent out in 1980 and 1990 and 14 500 responded to one of these. These questionnaires included detailed reports on health and risk factors.

Norwegian Family Based Life course Study Data from all 7,400 000 Norwegian citizens alive between 1960 to 2010 has been linked to family data and several health surveys and registers. Family linkage is available for more than 90 % of those born after 1940. This is linked to several other cardiovascular health surveys in addition to CONOR (in total 730,000) and the Conscript Registry.

Hospital discharges on cardiovascular diseases in Norway (FS-data): Data on all cardiovascular hospitalizations in Norway between 1994 and 2009 has been obtained through patient administrative systems at Norwegian hospitals. This includes coronary heart disease (both myocardial infarction and unstable angina), stroke and atrial fibrillation.

Social security registry (FD-trygd): Data on disability pension, sickness and social security benefits on all Norwegian citizens from 1992 onwards. Diagnosis will be ICD-10: F01-F99 (Mental, behavioral and neurodevelopmental disorders)

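### RQ 5 gives no way to tell family confounding from the extra attenuation that self-report error in drinking can cause within sibling and twin pairs

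*Protocol*

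**What the plan says.** Under *Approaches, hypothesis and choice of method*, the protocol sets the aim of finding "how much of the association between alcohol use and CVD may be accounted for by early life socioeconomic environment and shared family factors". It names two approaches, one of them the fixed-effect co-twin/sibling analysis. That paragraph labels the analysis RQ 4; the list of research questions makes it RQ 5.

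*Background and status of knowledge* shows how a result would be read. The team's earlier sibling study of education is cited as showing that much of a gradient "could be explained by family factors early in life shared by siblings". The protocol then suggests that "some of the estimated effect size both for moderate and binge drinking may be explained by early life confounding or family factors".

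Under *Statistical methods*, RQ 5 says that "the effects of alcohol consumption will be estimated by comparison between siblings or co-twins" and adds: "This approach effectively matches out all factors shared between siblings that may confound the effect of alcohol on cardiovascular mortality". The contrast drawn there is with studies of unrelated people. The research question itself says: "These results will adjust for early life and family factors".

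Under *Main variables*, exposure is self-report throughout. The twin registry (NTR) quantity item has three levels per beverage. CONOR binge drinking is a 12-month recall count (0 to 99), and NTR binge drinking is a frequency category. Reporting error is not mentioned in connection with RQ 5. The one reference to misclassification concerns whether binge effects are an artefact, not the pair contrast.

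**The concern.** A fixed-effect model yields a family share only by comparison: the effect among individuals against the effect within pairs. The gap equals the share due to shared factors if exposure is measured without error, or if error is as strongly correlated within pairs as true drinking.

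Relatives resemble each other in how much they drink. Differencing a pair therefore removes much of the true variation in exposure. If the two members misreport largely independently, the error stays. The within-pair contrast then has lower reliability than the individual measurement, and its log hazard ratio moves further towards zero. The more alike the pair, the larger this loss, so MZ twins lose more than DZ twins or siblings. Genetic or family confounding would produce the same ordering.

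At stake is the main conclusion of RQ 5. Part of the moderate-drinking or binge effect could be credited to upbringing or genes when it is measurement artefact. More data does not remove this bias.

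**Working it through.** **The plan's own figure.** The only number given for RQ 5 is 5050 CVD endpoints. It reproduces as 1400 (CONOR siblings) + 1700 (IHD) + 1950 (cerebrovascular), the last two from the 1980 NTR questionnaire. It has no bearing on attenuation.

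**Inputs**
- r, pair correlation of true drinking: not given. The proxy is the protocol's statement "Alcoholism is heritable (heritability 0.52-0.64", midpoint 0.58 for MZ pairs, and half of that, 0.29, for DZ pairs and siblings (the protocol says full siblings share 50% of the genes). Ranges: 0.52–0.64 and 0.26–0.32. This is heritability of alcoholism, so using it for ordinary drinking is an assumption.
- L, reliability of one self-report: not given; 0.5–0.9 is shown.
- re, pair correlation of reporting errors: not given; 0 first, then varied.
- Effects used as true values: relative risks 0.75 (average consumption) and 1.45 (binge), from the power section.

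**Formula.** Let reported drinking be true drinking (variance 1) plus error with variance (1−L)/L. The ordinary log hazard ratio is multiplied by L. The pair difference has true variance 2(1−r) and error variance 2(1−re)(1−L)/L, so the within-pair log hazard ratio is multiplied by

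Lw = L(1−r) / [L(1−r) + (1−L)(1−re)].

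The ratio of within-pair to ordinary effect is Lw/L. With re = 0 it becomes (1−r)/(1−L·r). The false family share is 1 − Lw/L.

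**Independent errors, no family confounding**

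| L | Siblings/DZ, r = 0.29 | MZ, r = 0.58 |
|---|---|---|
| 0.9 | 1 − 0.71/0.739 = 3.9% | 1 − 0.42/0.478 = 12.1% |
| 0.8 | 1 − 0.71/0.768 = 7.6% | 1 − 0.42/0.536 = 21.6% |
| 0.7 | 1 − 0.71/0.797 = 10.9% | 1 − 0.42/0.594 = 29.3% |
| 0.6 | 1 − 0.71/0.826 = 14.0% | 1 − 0.42/0.652 = 35.6% |

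Over the full r ranges and L from 0.9 down to 0.5, the false share runs from 3% to 19% in siblings/DZ pairs and from 10% to 47% in MZ pairs.

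**On the hazard ratio scale, L = 0.7.** For a true value of 0.75, the ordinary estimate is 0.75^0.7 = 0.818. Within pairs it is 0.833–0.838 (siblings/DZ) and 0.859–0.877 (MZ). For a true value of 1.45, the figures are 1.297, then 1.256–1.265 and 1.185–1.217.

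**Simulation check.** 400,000 pairs, true hazard ratio 0.75, no family confounding, about 14% events, ordinary against pair-stratified Cox model:
- Error-free exposure: 0.752 against 0.754 (r = 0.29) and 0.753 against 0.753 (r = 0.58), so no fall.
- L = 0.7: 0.819 to 0.841 (13% fall, closed form 11%) and 0.817 to 0.865 (29% fall, closed form 29%).

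**Correlated errors, L = 0.7, r = 0.58.** The ratio is 0.42 / [0.294 + 0.3(1−re)].

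| re | Ratio | False share |
|---|---|---|
| 0 | 0.42/0.594 | 29% |
| 0.2 | 0.42/0.534 | 21% |
| 0.4 | 0.42/0.474 | 11% |
| 0.58 | 0.42/0.420 | 0% |
| 0.7 | 0.42/0.384 | −9% (reversed) |

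**The case against.** The best case for the plan has four parts.

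**The attribution rule is inferred.** A reader might take the protocol to state that the fall will be reported as the family share, or that an MZ–DZ gradient will be read as genetic. It says neither. It speaks of adjusting for shared factors, and its claim that pairs match out shared confounders is true as far as it goes. This stands as a limit on wording. It does not remove the point: the aim is to find how much is accounted for, and a fixed-effect analysis answers that only through this comparison.

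**The direction is not certain.** A reader might infer that the bias always inflates the family share. It does so only if errors are less correlated within pairs than true drinking. Relatives may share habits of under-reporting, and the last table shows the artefact vanishing and then reversing. This stands.

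**The sizes rest on assumptions.** L, r and re are not in the documents, and a categorical or J-shaped exposure need not follow classical error. At L = 0.9 the sibling artefact is only 3–4%. This stands too.

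**Error correction belongs in a statistical analysis plan.** Its details do, and their absence is no fault here. The fault lies in an aim and an interpretation that the protocol itself sets.

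A reader might also want a false-positive rate for a test that the two effects are equal. The protocol plans no such test. For binge drinking, moreover, the 5,149 pairs of 1980 would be the wrong base, because they answered on moderate consumption. Binge data come from 2,138 pairs of 1990, with 900 + 1,040 = 1,940 expected cases. No such rate is claimed.

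**Conclusion.** The concern holds as a problem of identification. Nothing in the protocol separates shared family factors from the extra within-pair attenuation caused by reporting error, and its stated aim invites reading both as family factors. Under independent classical error, the false share at r = 0.29 (siblings/DZ) and r = 0.58 (MZ) is about 4% and 12% at L = 0.9, 11% and 29% at L = 0.7, and 14% and 36% at L = 0.6. It is smaller when errors are correlated and absent when re = r. These are illustrations under assumed parameters, not estimates for these cohorts. They do not show that family confounding is absent: real confounding and the artefact may both be present.

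**What to change.** Amend RQ 5 under *Approaches, hypothesis and choice of method* and under *Statistical methods*:

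- **(a)** Estimate the ordinary and the within-pair effects in the same twins and siblings.
- **(b)** Add a sensitivity analysis that does one of two things, not both. Either correct each estimate by its own reliability (L for the ordinary effect, Lw as above for the within-pair effect), or compare the observed ratio with the ratio expected from error. Doing both would count the correction twice. Run it over L of, for example, 0.5–0.9 and re from 0 up to r.
- **(c)** Attribute to shared family factors, or to an MZ–DZ gradient, only what remains across that range.

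For moderate drinking, twins who answered both NTR questionnaires could inform L, if there are any. The protocol says: "Questionnaires on alcohol consumption were sent out in 1980 and 1990 and 14 500 responded to one of these". If 14,500 means all who answered at least one, the counts imply at least 10,298 + 8,028 − 14,500 = 3,826 repeat respondents; the wording leaves this open. Ten-year agreement also contains true change, so use it only as a lower bound on L, and only if a person's errors in the two years are unrelated. NTR binge drinking is described for 1990 alone and needs the full range.

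The cost is a change of wording and a modest analysis on data already held. The downside is wider intervals and a more cautious statement of the family share.
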